This study is a prospective interventional study with minimal risks and constraints, not involving health products, according to the following points: "1. random allocation of procedure(s), or diagnostic or medical strategies or intervention(s) of current practice to a person or a group of persons" and "11. Interviews, observations and questionnaires, the results of which, in accordance with the protocol, may lead to changes in the participant's usual medical care and which therefore do not fall within the scope of the research mentioned in 3° of Article L.1121-1 of the Public Health Code" of the Order of 12 April 2018 establishing the list of research mentioned in 2° of Article L.1121-1 of the Public Health Code.

This study is a preventive study which forms part of the 6 fundamental skills of family practice*.*

The investigators are practitioners active in the field of primary care and networking ([name] [name], head of the university department of family practice in Brest):

- [name] heads an EA focusing on the study of Primary Care and Prevention in the general population (SPURBO) and has published a large amount of research on this subject.
- [name] has led a number of behaviour change groups at the diabetes network in Orléans and is an expert in motivational interviewing training.

These investigators, qualified persons in accordance with article 1122-1 of the Public Health Code, will be represented by family practice interns who will collect consent and data. These interns will be qualified persons under article 1122-1 of the Public Health Code, as they will have received appropriate training in the research protocol, as well as training in Good Clinical Practice and the use of the observation notebook, all under the aegis of the doctor-investigators and the Clinical Research and Innovation Delegation, which is ISO 9001-2015 certified for its activities in promoting and coordinating academic interventional clinical trials.

- 1. Primary endpoint

Comparison of the mean Non Laboratory Interheart risk score between the two arms at 24 months.

- 1. Secondary end points

Those secondary clinical endpoints will be measured at 24 months:

- Quality of life assessed by the WHOQOL brief scale,
- BMI reduction,
- Level of smoking (Reduction in the number of smokers/reduction in the number of cigarettes per smoker)
- Improving nutrition using the DASH Q,
- Level of physical activity using the IPAQ questionnaire,

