- Alcohol consumption by collecting declared weekly alcohol consumption.

Tertiary evaluation criteria :

- At 12 months :
- Non Laboratory Interheart risk score
- At 6, 12 and 18 months:
- Quality of life assessed by the WHOQOL brief scale,
- BMI reduction,
- Level of smoking (Reduction in the number of smokers/reduction in the number of cigarettes per smoker)
- Improving nutrition using the DASH Q,
- Level of physical activity using the IPAQ questionnaire,
- Alcohol consumption by collecting declared weekly alcohol consumption

Implementation assessment criteria at 6, 12, 18 and 24 months:

- Number of people screened, number categorised as green, orange and red.
- Number of people joining the SPICES programme (counted at the first SPICES meeting)
- Number of people carrying out the entire SPICES intervention (75% of all meetings)
- Cost of intervention
- Barriers and facilitators to intervention
- Qualitative assessment of screeners, intervention and resource persons

1. Study population
   1. Inclusion criteria

One group per phase :

- Screening phase :

From the general population, all people aged over 18 living or working in the Centre Bretagne region (including the Centre Ouest Bretagne, Pleyben and Callac regions).

- Randomised control trial (RCT) :

All people screened with a moderate cardiovascular risk score according to the Interheart clinical risk score (score of 9 to 15) in the screening phase.

- 1. Non-inclusion criteria

-For participants of the screening phase :

- Pregnancy
- Age under 18
- Patients undergoing secondary cardiovascular prevention
- People who do not live or work in Centre Bretagne (Pays Centre Ouest Bretagne and Pays de Pleyben et Callac)

For participants of the RCT, a low (<9) or high (>15) cardiovascular risk score according to the Interheart score.

- 1. Population description

People will be screened and recruited from the general population by trained members of the public with an interest in health promotion, named screeners.

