The data will be entered via the tablet, which will be used to calculate the Interheart score and define the tercile in which the participant’s risk score falls.

A brief advice linked to the participant's risk score will be automatically provided by the software.

The advice will be given immediately by the screener:

- For people whose score is in the lowest tercile (green score): no change in lifestyle and positive reinforcement,
- For people whose score is in the moderate tercile (orange score): advice on lifestyle changes and a proposal to join the Spices study (=intervention group).
- For people whose score is in the top tercile (red score): advice to change lifestyle habits and referral to the referring doctor.

The brief advice provided during screening will be standardised minimum advice in line with the latest recommendations and will be identical in the two steps. It will include the health messages disseminated to the general public by the national plans identified during the situational analysis carried out at the start of the project (Programme national de réduction du tabagisme (PNRT); Programme national nutrition santé (PNNS); Plan Santé sport bien-être (SSBE); Plan national santé environnement (PNSE); Plan de santé au travail; Plan Accident Vasculaire Cérébral (Plan AVC); Plan Obésité).

Example: *« You have declared that you are an active smoker. Quitting smoking will reduce your risk of cardiovascular disease. You have stated that you do not eat enough fruit and vegetables. Eating fruit and vegetables every day will reduce your risk of cardiovascular disease. »*

The screeners will be supported during the intervention by family medecine interns under the supervision of the research team. These family medecine interns at the Faculty of Brest will be working on this project as part of their mandatory master thesis.

- 1. Follow-up of people screened for moderate cardiovascular risk
     1. Control/Intervention groups

After screening, the research team will contact people with a moderate CVDR (Non Laboratory InterHeart risk score orange from 9 to 15 included) to include them into the SPICES study and to randomise them. The software will random participants in either the control group or the intervention group.

Regardless of randomisation, participants will be individually interviewed by a member of the research team, who will measure the clinical endpoints at time zero of the intervention, and then at 6, 12, 18 and 24 months.

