  - Hierarchical analysis in two steps: 1) comparison of the mean Interheart between the two arms at a risk of alpha=0.05, then in the event of a statistically significant result 2) comparison of the 6 secondary endpoints between the two arms, using the Holm-Bonferroni correction to take account of the multiple comparisons carried out in this step. In accordance with the principles of hierarchical analysis, the tests in step 2) can only be performed demonstratively if the test in step 1) is statistically significant (p<0.05).
- Quantitative endpoints will be compared between the two arms using a Student's t test. Qualitative endpoints will be compared between the two groups using a Chi-2 test. Multivariate analyses will be performed secondarily using a linear model to adjust for potential confounding factors.
  1. Expected number of people to be included in the research, and expected number of people in each research location with statistical justification

The calculation of the number of participants is based on the comparison of the mean Interheart between the two arms: for a power of 80%, a risk alpha=0.05 and an effect size (mean difference / standard deviation) of 0.20 the number of participants required is 394 per arm. Including approximately 20% lost to follow-up, a total of 985 participants should be included. With a number of participants of 394 patients per arm and the assumption of an effect size of 0.20 for each secondary endpoint, the test power is approximately 68% for each secondary endpoint using the Holm-Bonferroni correction to account for multiple comparisons.

- 1. Method for taking into account missing, unused or invalid data

Missing data will be identified via the electronic CRF, and the investigators will be called back to complete the data. Incomplete files will be declared lost to follow-up.

1. Right of access to data
   1. Access to data

In accordance with GCP :

- the sponsor is responsible for obtaining the agreement of all parties involved in the research in order to guarantee direct access to all research sites, source data, source documents and reports for the purposes of quality control and audit by the sponsor,

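### The deciding 24-month comparison is an unadjusted t test although every participant has a screening Interheart score, so a modest and nearly free gain in precision goes unused

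*Protocol*

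**What the plan says.** Protocol section 4.2 defines the primary endpoint as "Comparison of the mean Non Laboratory Interheart risk score between the two arms at 24 months". Section 8.1 names the test: "Quantitative endpoints will be compared between the two arms using a Student's t test". It then places adjustment second: "Multivariate analyses will be performed secondarily using a linear model to adjust for potential confounding factors". No covariate is named there, and the screening score appears in no primary model.

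Section 8.1 also sets a two-step hierarchy: "comparison of the mean Interheart between the two arms at a risk of alpha=0.05, then in the event of a statistically significant result", the six secondary endpoints are compared with a Holm-Bonferroni correction.

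Section 8.2 sizes the trial on the same unadjusted comparison, "for a power of 80%, a risk alpha=0.05 and an effect size (mean difference / standard deviation) of 0.20", and concludes that "the number of participants required is 394 per arm". Allowing for about 20% loss brings the total to 985.

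On the baseline value, section 5.1 restricts the randomised trial to people who scored 9 to 15 at screening. Section 6.1 says how that score is obtained: "The data will be entered via the tablet, which will be used to calculate the Interheart score". Section 6.2 lists the measures taken at time zero, and Interheart is not among them. The baseline value of the primary endpoint is therefore the screening score, obtained before randomisation.

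**The concern.** Two people with different screening scores are likely to differ at 24 months whichever arm they are in. An unadjusted comparison counts that predictable spread as noise. A model that includes the screening score removes it, narrows the confidence interval, and corrects for any chance difference between the arms at entry.

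The reason the protocol gives for adjustment also misses this benefit. Under individual randomisation, baseline variables are not confounders in expectation. The case for including the screening score is that it predicts the outcome, and that argues for using it in the primary test.

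This is more than a detail left to a statistical analysis plan. The protocol itself names the primary test and ranks the adjusted model below it, so an analysis plan that made the adjusted model primary would contradict the protocol. The stake is the power of a test designed at only 80%, on which any confirmatory claim for the six secondary endpoints also depends.

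**Working it through.** **Step 1: reproduce the plan's figures.** Inputs from section 8.2: effect size 0.20, alpha 0.05 (taken as two-sided, since this reproduces the stated number), power 80%, loss 20%.

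- The t-based sample size is 393.4, rounded up to 394 per arm. The normal approximation gives 393.
- Total: 2 × 394 / 0.80 = 788 / 0.80 = 985.
- Power at 394 per arm, normal approximation: Φ(0.20 × √(394/2) − 1.96) = Φ(2.807 − 1.96) = 80.2%. The t-based value is 80.1%.

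The figures reproduce exactly, so the design takes no credit for the screening score.

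**Step 2: effect of adjustment.** With correlation r between screening and 24-month scores *among those randomised*, adjustment multiplies the variance by (1 − r²). Power becomes Φ(2.807/√(1 − r²) − 1.96).

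**Step 3: a plausible r.** The protocol gives no value. Restricting entry to 9 to 15 shrinks the correlation seen in the whole screened population (R). Section 6.1 calls this band the moderate tercile, and section 14 expects one third of those screened to fall in it. As an illustration, assume a normally distributed score with the middle third enrolled. The variance of the screening score inside the band is then u = 0.0603 of its full-range value, and

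r = R√u / √(R²u + 1 − R²).

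For R = 0.6: 0.6 × 0.2456 / √(0.36 × 0.0603 + 0.64) = 0.147 / 0.813 = 0.18.
For R = 0.8: 0.8 × 0.2456 / √(0.64 × 0.0603 + 0.36) = 0.196 / 0.631 = 0.31.

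| Full-range R (assumed) | In-band r | Power at 394 per arm | n per arm for 80% |
|---|---|---|---|
| no adjustment | – | 80.2% | 393 |
| 0.5 | 0.14 | 80.9% | 385 |
| 0.6 | 0.18 | 81.4% | 380 |
| 0.7 | 0.23 | 82.3% | 371 |
| 0.8 | 0.31 | 84.0% | 355 |
| 0.9 | 0.45 | 88.2% | 313 |

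For R from 0.6 to 0.8, the gain is worth 393 − 380 = 13 to 393 − 355 = 38 participants per arm. The confidence interval narrows by about 2% to 5%, since √(1 − r²) is 0.98 to 0.95.

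**Step 4: larger values, for range.** In-band r = 0.4 gives 2.807/√0.84 = 3.063 and power 86.5%. In-band r = 0.5 gives 2.807/√0.75 = 3.241 and power 90.0%.

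**The case against.** The strongest reply is that nothing here is wrong. With individual randomisation the t test is unbiased, the sample size matches it, and an adjusted model is already planned. All of that stands. A reader might infer that the primary analysis is invalid or underpowered, and the documents support neither. A reader might also infer that the protocol leaves open which result decides the trial if the adjusted and unadjusted ones disagree. It does not: section 8.1 makes the first-step comparison decisive and the adjusted model secondary.

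The second reply concerns size, and it also stands. Assuming a full-range standard deviation of 4 to 6 points and R of 0.6 to 0.8, one can obtain an in-band correlation of 0.24 to 0.54, and so power near 90%. For a normal score centred on the band, however, those standard deviations put 44% to 62% of people inside it, which conflicts with the one third that section 14 expects.

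Two further inferences lack support. One is that the correlation must be high because fixed items such as family history, diabetes and hypertension are part of the score. Section 6.1 gives only the number of items, and section 6.4 lists family and personal history without marking them as Interheart items. The other is that adjustment would make up for power lost because the intervention is delivered in groups. The protocol gives no intra-group correlation, so that comparison cannot be made.

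None of this removes the point. The covariate is on file for everyone, any non-zero correlation gives a gain, and only the protocol can change which test is primary.

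**Conclusion.** The point holds as one of efficiency, not validity. The protocol fixes an unadjusted test as decisive and sets aside a pre-randomisation measurement of the same outcome that every participant must have. On the protocol's own description of the eligible band, and with an assumed full-range correlation of 0.6 to 0.8, the forgone gain is about 1 to 4 power points (from 80% to 81% to 84%). The illustration also assumes a normally distributed score. Gains to 86% to 90% need an in-band correlation of 0.4 to 0.5, which the protocol gives no reason to expect. The size is therefore uncertain and probably modest. The direction is not in doubt, and the change is worth making because it costs so little.

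**What to change.** In section 8.1, make the primary analysis a linear model of the 24-month Interheart score on arm, adjusted for the screening Interheart score. Describe that covariate as prognostic rather than as a confounder. Keep the Student's t test as a sensitivity analysis. A t test on change from screening is not an equivalent substitute: it fixes the coefficient of the screening score at 1 instead of estimating it, and so cannot be expected to be more precise.

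Analyse each continuous secondary endpoint as its 24-month value adjusted for its own time-zero value. Section 6.2 does not say whether time-zero measures are taken before the allocation is known, so the text should state that they are. Name any further covariates in advance and limit them to pre-randomisation variables.

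The sample size can stay as it is, with the gain kept as a margin. The cost is one degree of freedom out of about 786 and a change of wording; no new data, visits or participants are needed. If the change is classed as substantial, section 11.2 requires sponsor approval and a favourable ethics committee opinion before it takes effect. It should be settled before any 24-month comparison by arm is made.

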The investigator will inform each participant prior to inclusion in the trial, full and adequate verbal and written information regarding the objective and procedures of the trial and the possible risks involved, the necessary surveillance and safety measures, their right to refuse to participate in the study or the possibility of withdrawing at any time.

For people screened (the general population of the COB area), this information will be given orally and a general information letter such as a leaflet or flyer will be sent to them.

For people recruited with a moderate CVDR, all the information is given on an information and consent form given to the participant. The participant's free, informed and written consent will be obtained before definitive inclusion in the study by the trainer who will represent one of the 3 doctors declared as investigators. These community champions will all have received appropriate training, validated by a certificate giving them the authority of the declared investigators to present and sign the consent form.

A copy of the information and consent form signed by both parties will be given to the participant, and the trainer will keep a copy.

As this study is taking place in the general population, all the participants recruited will depend on the 3 declared investigators.

1. **Data recording and processing**
   1. Observation book electronic

All the information required by the protocol must be recorded in the observation books. Data should be collected as it is obtained and recorded explicitly in the notebooks. Any missing data should be coded.

This electronic observation book will be accessible via an Internet data collection medium provided to community champions.

If the research team fills in the case report form via the Internet, the CRA can view the data quickly and remotely. The investigator is responsible for the accuracy, quality and relevance of all data entered. In addition, when data is entered, it is immediately checked for consistency. As such, he must validate any change in value in the CRF. These changes are subject to an audit trail. A justification may be included as a comment.

A pdf copy of the observation notebooks signed by the investigator will be saved and given to the investigator for archiving.

- 1. Data input and output

Data will be entered electronically via the web browser RedCap.

- 1. Data protection authority (CNIL)

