As this study requires the community champions to contact patients with moderate cardiovascular risk at the end of the screening period, it is necessary for the research team to have the full identity of the participants, as well as their telephone and postal contact details. This identifying data, which is strictly necessary for carrying out the research, will be kept only until the end of the study and will be accessible only by the research staff. The "Reference Methodology" (MR-001 - N°1749494v0 dated 11/03/2014) in application of the provisions of article 54 paragraph 5 of law n°78-17 of 6 January 1978 as amended therefore applies to this project.

- 1. Archiving

All study data will be stored in the investigating centers and on the sponsor's premises in accordance with the current regulations.

1. Insurance

The Sponsor will take out insurance covering its own civil liability and that of any doctor involved in carrying out the study, for the entire duration of the study. It will also provide full compensation for the harmful consequences of the research for the person who takes part in it and their dependants, unless it can prove that the damage is not attributable to its fault or to that of any other party involved, without any claim being made against it on the grounds of a third party or the voluntary withdrawal of the person who initially agreed to take part in the research.

1. Feasibility

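### The protocol names conflicting people for contact and consent, labels the study offer as the intervention group, and does not place the baseline interview before allocation

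*Protocol*

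**What the plan says.** On consent, section 11.3 states that "informed and written consent will be obtained before definitive inclusion in the study by the trainer", and adds that the community champions are certified to present and sign the form. The synopsis says that trainers and community champions are the same people, and section 6.3 has them lead the behaviour change sessions. Section 4.1 says instead that the investigators "will be represented by family practice interns who will collect consent and data".

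On first contact, sections 6.1 and 6.2.1 have the research team approach people at moderate risk. Section 12.3 justifies holding identifying data with "As this study requires the community champions to contact patients with moderate cardiovascular risk at the end of the screening period".

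On the offer, section 6.1 lists what the screener gives a person with an orange score: lifestyle advice and "a proposal to join the Spices study (=intervention group" (the parenthesis closes there). Sections 6.1 and 6.2.1 then randomise these people to control or intervention.

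On sequence, section 6.2.1 describes contact, inclusion and allocation by software, and continues: "Regardless of randomisation, participants will be individually interviewed by a member of the research team, who will measure the clinical endpoints at time zero". The sentence goes on to define that time zero by the intervention and to list visits at 6, 12, 18 and 24 months. The measures are WHOQOL, weight, height and BMI, smoking, DASH-Q, IPAQ and declared alcohol intake. The Interheart score is not on this list; sections 6.1 and 6.2.1 place it at screening, before randomisation.

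**The concern.** Three things in an individually randomised, open behavioural trial should be beyond doubt: who recruits, what the candidate is offered, and whether baseline is complete before anyone learns the allocation. The protocol settles none of them.

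Two harms could follow. First, if the baseline interview takes place once allocation is known, self-reported answers on diet, activity, smoking, alcohol and quality of life may shift with that knowledge. Any secondary endpoint expressed as a change from baseline then carries the shift. Second, someone who joins expecting the programme, and is then allocated to brief advice already received at screening, has a reason to leave. Section 8.3 declares incomplete files lost to follow-up, so such losses could fall unequally on the two arms.

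**Working it through.** **The plan's own figures.** Section 8.2 sizes the trial "for a power of 80%, a risk alpha=0.05 and an effect size (mean difference / standard deviation) of 0.20". Sidedness is not stated; two-sided reproduces the result.
- Per arm, normal approximation: 2 × (1.960 + 0.842)² / 0.20² = 2 × 7.849 / 0.04 = 392.4, so 393. The exact t-test solution is 393.4, so 394, as stated.
- Total: 2 × 394 = 788, and 788 / 0.80 = 985, as stated. The allowance for loss is 985 − 788 = 197 people, with no split by arm.
- Secondary endpoints: simulated Holm-Bonferroni power over six endpoints at 394 per arm and effect 0.20 is 68.6% if they are independent and 65.7% at a correlation of 0.8. The stated figure is about 68%.

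These figures reproduce. None has the consent-taker or the timing of baseline as an input, so the rest is a comparison of texts.

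**The texts side by side.**

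| Question | One reading | Other reading |
|---|---|---|
| Who makes first contact? | Research team (6.1, 6.2.1) | Community champions (12.3) |
| Who takes written consent? | Family practice interns (4.1) | Trainers, i.e. community champions (11.3, synopsis) |
| What is offered at screening? | Randomisation to either group (6.1, 6.2.1) | The intervention group (parenthesis in 6.1) |
| When is the secondary baseline taken? | Not stated to precede allocation | Described after randomisation and tied to the intervention (6.2.1) |

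The first three rows are contradictions. The fourth is an inference from text order: the phrase about randomisation in 6.2.1 says that both arms are interviewed alike and does not itself fix a sequence. No sentence says that baseline is complete before allocation is released. Time zero is also defined by an intervention, while controls receive brief advice only (6.2.2), so the date from which their visits run is not specified.

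**Which analyses are exposed.**
1. The primary endpoint is the mean Interheart score at 24 months (4.2), compared by a t test, with adjusted models only secondary (8.1). No baseline value enters that test, and the Interheart score at entry precedes randomisation.
2. Of the six secondary endpoints in 4.3, BMI and smoking are worded as reductions and nutrition as improvement. Smoking and nutrition rest on self-report. Quality of life, physical activity and alcohol have self-reported baselines too, and would be exposed if analysed as change.
3. Differential dropout is the route by which the primary comparison could be touched, because people who leave have no 24-month score. That needs losses that differ by arm and relate to outcome.

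**The case against.** The strongest reply is that these are drafting slips and that the safeguards which matter are present. Software allocates. The text says include, then randomise. Consent comes before inclusion is final. The champions are drawn from the screeners, who are trained to include moderate-risk people (synopsis), so they have a recruiting role that does not depend on arm. Section 6.2.1 gives both arms one visit schedule. The parenthesis in 6.1 is protocol text, not the words spoken to a candidate, and section 11.3 requires full written information before inclusion.

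Most of this stands. A reader might infer that a champion who takes consent must know the allocation, or that concealment has failed. The documents do not support that: nothing says a champion can see or predict the next assignment. A reader might also infer that the arms are not comparable at entry on the primary variable. That fails too, because the Interheart score is obtained at screening.

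What the reply does not remove is the conflict over contact and consent, the mislabelled offer in the section that instructs the screeners, and the absence of any statement that the baseline interview is complete before allocation is revealed. These are matters of conduct that a statistical analysis plan would not ordinarily settle.

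**Conclusion.** The point holds as a set of contradictions and an unfixed sequence that leave two things unprotected: the largely self-reported secondary baselines and the retention of controls. It is not a finding that concealment is broken or that the primary baseline is compromised, although the text could tempt a reader to either conclusion.

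The size cannot be computed. The protocol gives no rate of refusal or dropout by arm and no estimate of how far reporting might shift with allocation. By the wording of section 4.3, at least two self-reported change-type endpoints, smoking and nutrition, are exposed. The stated sample size and power are unaffected.

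The conclusion assumes that the text order in 6.2.1 reflects practice. If the baseline interview in fact precedes allocation, the baseline concern disappears and only the wording needs repair. The dropout concern assumes that screeners convey the offer as section 6.1 labels it.

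**What to change.** Reconcile sections 4.1, 6.1, 6.2.1, 11.3 and 12.3 into one sequence:
1. contact by a single named role;
2. written consent;
3. the full time-zero interview;
4. software release of the allocation, only after the baseline form is locked.

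Count 6, 12, 18 and 24 months from the randomisation date in both arms. Delete the parenthesis in 6.1 and state that candidates may be allocated to either group.

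Name one consent-taker. Where existing staff allow, this should be someone who will not deliver the intervention to that participant; in any case, consent should be taken before allocation is known. Simply choosing interns over champions does not achieve the separation, because section 6.3 has interns help run the groups.

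The cost is amendment wording, with the approvals that section 11.2 requires for a substantial modification, and a lock on the randomisation step. No visit is added, since the same interview is placed before randomisation. The number of interns is not given, so the effect of any transfer of consent on workload cannot be judged. A small downside is that some people assessed at baseline will not be randomised.
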